When prescribing, it is important that prescribers are aware of all medications, including non-prescription, in order to prevent interactions or to identify possible side effects: so, it is essential to support actions that allow pharmacists to share the information gathered through a medication review. It could be reach though the implementation of a shared electronic medication plan. Hence, it is important to develop a service that allows the inclusion of the most accurate information on all the medications a patient is taking on such a shared patient’s medication plan.

The Cantonal Health Authorities of Vaud in collaboration with the Cantonal pharmacists association and the Center for Primary Care and Public Health of the University of Lausanne (Unisanté) developed an initiative for a medication review type 2A [17] with follow up (MRF) service. MRF includes follow up due to the results found in the literature, which suggests that medication review with follow up reduces patients’ problems related with the use of medicines [18]. The aim of such service is to perform a medication review at the CP to 1) prevent, identify and manage DRPs related to patients due to the lack of such service in Switzerland, 2) improve patients’ knowledge about their treatments and 3) remove of expired medications for proper elimination by the CPs. Based on the principles of the “brown bag” [19–21] and medication review with follow up [18, 22], MRF includes all the treatments consumed by the patient (prescription and non-prescription medication). This service allows the pharmacists going further than usual prescription validation in terms of detection of DRPs and pharmaceutical interventions. MRF offers the opportunity for the identification and management of DRPs related to patients, the assessment of all medication, disposal of expired medications and the detection of patients’ lack of knowledge about their treatments. For this, the patient brings the medication to the CP before performing the service. MRF also strengthens the role of pharmacy technicians to perform an initial sorting of the medication brought to the CP to divide prescription and non-prescription and to eliminate expired medication. Therefore, allowing pharmacists an optimal use of the time devoted to the consultation. The service is in line with the national objective to reinforce pharmacy technicians’ role, their education and to allow them to assist (under supervision) some services [23].

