### Sample size

Primary objective of the study aims to measure the difference in DRPs per patient observed between consultations. Sample size calculation was based on this primary study outcome to detect a difference of 0.5 DRP per patient at the end of the study (using a one-tailed test because the hypothesis is that patients will have a decrease of DRPs at the end of the study). The calculation was based on a pilot study carried out on 20 patients at Unisanté CP. Sample size was calculated with ≥0.8 power, type I error rate of 5%, assuming an intra-cluster correlation of 0.02. Allowing for 15% dropout, the overall sample size is 162 patients, with 19 to 35 pharmacies (5–10 patients per CP).

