### Statistical methods and analysis

Continuous variables will be summarized using mean and standard deviation, or median and percentiles depending on the distribution of the variable. To assess normality, the Kolmogorov Smirnov test will be used. Categorical variables will be reported by frequency and proportion. For the comparison of continuous variables, the T Student’s test or the ANOVA test will be carried out if there is a normal distribution, and Kruskal-Wallis otherwise. The comparison of the categorical variables will be carried out using the χ2 test, the Fisher’s exact test or Yate’s chi-squared test if necessary.

For each patient, differences between consultations (second and first consultations, third and first consultations) will be compared for dependent variables (number of DRPs and medication expired, patient knowledge score, pharmaceutical interventions and medication removed, proportion of pharmaceutical interventions acceptance). A linear regression model will be performed accounting for the cluster effect. A cluster effect is expected by the way pharmacists interact with their team and the surrounding GPs, this could influence the number and type of DRPs detected and interventions made. A sub analysis will be carried out to evaluate the effect of patients undertaking or not a pre-selection of their medication before attending the pharmacy. Firstly, variables will be considered significant (p-value<0.2) in a bivariate model to be included in a multivariate model. Secondly, the variables considered significant at a value of p<0.1 in the multivariate model will be included in the final model. The level of significance will be set at p<0.05; the software STATA 17® will be used. An analysis with completed cases will be made (patients with data for the three consultations). In addition, an analysis with the whole sample will be made where, for the management of missing data, initial value will be considered as not been modified (baseline observation carried forward-BOCF) [28]. In case of a sufficient number of patients who are 65 years old or over are randomly included in the study, a sub analysis will be carried out to target the intervention to a specific group of patients with higher risk for DRPs [29, 30].

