Some limitations to the study should be discussed. First, the study will be conducted in the canton of Vaud, thus, the results obtained may not be applicable to the rest of Switzerland. Indeed, national (federal) but also local (cantonal) laws and ordinances govern pharmacy practice in Switzerland. Thus, it must be applicable with some considerations especially for those regions where the GP prescribes and dispense medication (currently performed in some German speaking cantons) [39]. To minimize the impact on the generalization of the results obtained to the target population, as it have been noticed in the literature [40], patients included in the study will be randomly preselected by the research team (to avoid selection bias by pharmacists selecting only patients who are more likely to have better results). Second, the patient may not bring all the medications at the time of the consultation, which could lead to an underestimation of the identification of DRPs. However, pharmacy technicians will insist in the importance of reviewing all the medication with the patient. Third, dropouts are expected due to the number (three) of consultations with the patient and the duration of the study (fifteen months), although different analysis will be carried out (complete cases and all sample) to study possible differences and bias. Also, considering there will be a pre-post measurement of outcomes with no control group, it will not be possible to compare the MRF service directly to the current Swiss pharmacy practice. Nonetheless, outcomes will be measured at 6-month intervals, which will allow establishing if the impact of the MRF service varies across time. And lastly, as any other study, the Hawthorne effect may influence patients and pharmacists, that is, the effect of being studied which can potentially impact on participants’ behavior.

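### Complete cases plus BOCF is a weak pair for missed consultations: BOCF dilutes the change in DRPs, and comparing the two says little about dropout bias

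*Protocol article*

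**What the plan says.** Under Statistical methods and analysis, the dependent variables are compared as within-patient differences: second minus first consultation, and third minus first. A linear regression accounts for clustering by pharmacy. Two rules for missing visits follow. The first is "An analysis with completed cases will be made (patients with data for the three consultations"; the second covers the whole sample, where the "initial value will be considered as not been modified (baseline observation carried forward-BOCF" rule applies. No outcome in the list is exempted from that rule. The list includes DRPs, expired and removed medication, knowledge score, interventions and the proportion of interventions accepted.

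The limitations text (Discussion, Comparison with literature) expects dropouts and answers "although different analysis will be carried out (complete cases and all sample) to study possible differences and bias". The Sample size section allows for 15% dropout and aims "to detect a difference of 0.5 DRP per patient at the end of the study".

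**The concern.** The size of the fall in DRPs is the primary objective. There is no control group, so nothing offsets a distortion of the pre-post change.

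- **Imputed zeros.** When the outcome is a change from the first consultation, carrying the first value forward means entering zero as if it had been observed.
- **The bias check.** The limitations text treats agreement or disagreement between the two analyses as evidence about dropout bias. If one result is largely a rescaling of the other, the gap mainly reflects how many patients left, not how they differed.
- **Lost 6-month data.** The complete-case rule requires all three visits. In that analysis, a patient who misses only the third visit also loses an observed 6-month change.
- **Outcomes with no sensible baseline to carry.** Table 1 has intervention acceptance recorded only at the second and third consultations, so no first value exists. For interventions, BOCF would credit activity at a consultation that did not take place. For removed medication, it would count again items the patient has already agreed to give up.

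**Working it through.** **Inputs from the article (Sample size).** Target fall 0.5 DRP; N = 162; 15% dropout; one-sided test ("using a one-tailed test because the hypothesis is that patients will have a decrease of DRPs at the end of the study"); "Sample size was calculated with ≥0.8 power, type I error rate of 5%, assuming an intra-cluster correlation of 0.02". The SD of the change is not given and has to be assumed.

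**The plan's own figure.** Without an SD, 162 can be neither confirmed nor refuted. Solving n = DEFF × [SD × (1.645 + 0.842) / 0.5]² for SD, with n = 0.85 × 162 = 137.7 and DEFF = 1 + (m − 1) × 0.02:
- m = 10, DEFF 1.18: SD ≈ 2.17
- m = 5, DEFF 1.08: SD ≈ 2.27

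If 162 is the number before dropout, SD is 2.36 to 2.46. A value near 2.2 is used below, with 1 to 3 as the range.

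**Step 1: BOCF estimate and standard error.** Let a share d of changes be set to 0, with dropouts otherwise like completers.
- Estimate: (1 − d) × 0.5 = 0.85 × 0.5 = 0.425
- BOCF SE: √{[(1 − d)SD² + d(1 − d)0.5²] / 162}
- Complete-case SE: SD / √137.7
- Approximate coverage of the true change by the BOCF 95% interval: Φ(1.96 − b) − Φ(−1.96 − b), with b = 0.075 / BOCF SE

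| SD of change (assumed) | Complete-case SE | BOCF SE | Ratio | Coverage |
|---|---|---|---|---|
| 1 | 0.085 | 0.074 | 0.866 | 0.83 |
| 2.2 | 0.187 | 0.160 | 0.853 | 0.92 |
| 3 | 0.256 | 0.218 | 0.852 | 0.94 |

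These formulas ignore clustering. Simulation with ICC 0.02, cluster-robust SEs, random dropout, 18 × 9 or 27 × 6 patients, 8,000 runs per setting and SD 2.0 or 2.2 gave coverage of 0.919 to 0.933 for BOCF, against 0.948 to 0.951 for complete cases.

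**Step 2: does the test suffer?** At SD 2.0 with 18 × 9 patients, the mean BOCF SE was 0.153 and the true sampling SD of the BOCF estimate was 0.154. Power was 0.845 (BOCF) against 0.847 (complete cases). With no true change, one-sided rejection over all settings was 0.047–0.052 against 0.046–0.051. Estimate and SE shrink together, so the t statistic is 0.98 to 1.00 times the complete-case value.

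**Step 3: what the comparison can show.** Under monotone dropout, everyone seen at the third visit is a complete case. The unadjusted third-visit BOCF mean is then [137.7 × (complete-case mean) + 24.3 × 0] / 162 = 0.85 × the complete-case mean, whatever the missing patients were like.

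**Step 4: dropout that depends on baseline DRPs (illustration).** Assume SD 2 per visit and correlation 0.4 between visits, so the SD of change is √[2 × 4 × (1 − 0.4)] = 2.19. Assume a true fall of 0.50, 15% dropout, dropout log-odds changing by 0.5 per baseline DRP, and no clustering. The slope of change on baseline is 0.4 − 1 = −0.6. Integrating over this dropout model puts the completers' mean baseline 0.27 DRP from the full-sample mean.
- High-DRP patients leave more: complete cases 0.50 − 0.6 × 0.27 = 0.34; BOCF 0.85 × 0.34 = 0.29.
- Low-DRP patients leave more: complete cases 0.50 + 0.6 × 0.27 = 0.66; BOCF 0.85 × 0.66 = 0.56.

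A likelihood estimate on all observed visits recovered 0.50 in both cases. When dropout depended only on the second-visit count, complete-case bias was negligible.

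**The case against.** The strongest reply is that BOCF leans towards no effect, is reported beside complete cases and leaves the test intact. Much of that stands, and it limits what can be claimed.

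- A reader might infer that the BOCF standard error is about 15% too small. It is about 13–15% smaller than the complete-case SE, but it is the right SE for BOCF's own diluted estimator. False significance does not follow.
- A reader might infer that 6-month data are discarded altogether. They are lost only in the complete-case analysis; the whole-sample analysis keeps a patient's observed second-visit change.
- A reader might infer that the comparison can never detect bias. The 0.85 identity is exact only for the unadjusted third-visit mean under monotone dropout. It breaks if patients miss the second visit and return, and it need not hold for the 6-month contrast.
- A reader might infer that BOCF is known to be false for expired medication. The Introduction's "remove of expired medications for proper elimination by the CPs" states an aim of the service. Table 1 counts removals accepted by the patient separately, and further items can expire between visits. Carry-forward is implausible for accepted removals, which is a narrower point.
- Dilution is not certain. If dropouts truly did not change, BOCF is right; if they worsened, it is too favourable.

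The 15% is also a planning figure. Data of patients who withdraw consent are destroyed (Ethics approval and safety considerations), so they are not imputed and the imputed share may be lower. A separate analysis plan, not seen here, may add methods.

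**Conclusion.** The concern holds as a weakness in the chosen methods, not as an error in the test. At 15% dropout, and if dropouts would have changed like completers, BOCF reports 0.425 for a true fall of 0.50. Its 95% interval covers the truth about 92–93% of the time at an SD of change of 2.0 to 2.2; without clustering, the figure runs from about 83% to 94% over SD 1 to 3.

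The planned comparison of the two analyses is a poor check on bias, because under monotone dropout it mostly returns the dropout rate. Both analyses can miss in the same direction if dropout depends on baseline DRPs. The figures 0.34/0.29 and 0.66/0.56 rest on the assumed SD, correlation and dropout strength, so they illustrate the mechanism and do not forecast the bias in this trial.

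**What to change.** Make the main analysis one mixed model on all available consultations: visit (1, 2, 3) as fixed effect, a random intercept for pharmacy, and a patient-level covariance across the three visits, preferably unstructured. Random intercepts alone would force equal correlation between all pairs of visits. The main contrast is visit 3 minus visit 1, with visit 2 minus visit 1 from the same model.

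Keep complete cases and BOCF as sensitivity analyses, and describe them as such in place of the claim that their comparison studies bias. Do not apply BOCF to removed medication, to interventions at consultations that did not take place, or to acceptance.

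The cost is a revised analysis paragraph and a standard Stata command; no new data are needed. The downside is modest: the model relies on data being missing at random given the observed values, and its covariance structure has to be specified in advance.

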### Data management

Champion pharmacists are responsible for keeping all documents in their CP according to current legal practices and requirements. The different forms used during the study will be recorded in the pharmacy using an electronic format (Microsoft Excel®) and they will be coded. Study data will be collected and managed using Research Electronic Data Capture (REDCap 12.5.4© 2022 Vanderbilt University) hosted at Unisanté [31] to improve data privacy and data reliability. Data will be double checked by an external data processing agency to assure codification is being done correctly by pharmacists. Afterwards, data will be accessible by the research team at Unisanté via RedCap®. Data will only be accessible by the researchers involved in the project and will be hosted on Unisanté’s server (backed up electronically). At the end of the study, data will be kept up to 10 years after the last publication.

### Status and timeline

Data collection started in April 2023. Statistical analysis will be completed in summer 2024. Following this, the findings will be disseminated through a final report and communications to the health professionals and general population. In addition, congress communications and peer-review publications in scientific journals. It is also a will of the local association and authorities to continue with the service after the study.

### Ethics approval and safety considerations

The study was approved by the Cantonal Commission for Ethics in Human Research (CER-VD) (registration number 2023–00139, protocol version 04, 21.03.2023) (S5 Appendix). Participants will give oral consent; a patient could withdrawal from the project due to removal of informed consent, change of the community pharmacy (for a pharmacy not involved in the project, i.e., out of the Canton), absence to pharmacist-patient consultations, or death. In case of withdrawal of informed consent, data will be destroyed (by identifying patient’s Id), therefore patient’s data will not be used in the analysis and study results.

### Trial registration

The protocol of the study was registered on ClinicalTrials database in May 2022 under the number NCT05348538. In addition, S6 Appendix includes the items from the World Health Organization Trial Registration Data Set.

## Discussion

The present protocol describes the design of a pre-post intervention study in Swiss CP to determine the impact of an enhanced service (Fig 2), which is defined as service that “transcend conventional requirements of an outpatient pharmacy program contract that are focused on improving clinical and global patient outcomes” [32], for MRF in order to detect DRPs. The study reports one primary outcome measure, the identification and management of DRPs related to patients with polypharmacy.

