**Methods:**

A pre-post intervention study with a cluster design and one intervention group will be carried out in CPs in the canton of Vaud (Switzerland) for 15 months. Volunteer pharmacists will be trained on the identification and management of DRPs related to patients’ behavior. After training, they will include randomly selected adults taking four or more chronic drugs prescribed for at least three months prior to recruitment. Then, they will conduct three pharmacist-patient face-to-face consultations at 6-month intervals. Tasks will be differentiated by pharmacy technician or pharmacist to triage expired medication or to manage DRPs in a structured manner, respectively. The primary outcome is the identification of DRPs associated to patients’ behavior. Secondary outcomes are to assess patients’ medication knowledge, number of expired medications, interventions carried out by pharmacists and pharmacists’ satisfaction. The study will begin in April 2023 in 19 to 35 pharmacies that will recruit at least 162 patients. A sub analysis will be carried out for patients with 65 years old or over.

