### Study measurements and outcomes

Dependent study outcomes and variables are presented in Table 1. In addition, independent variables will be collected in relation to patients (socio-demographic characteristics variables: gender, year of birth and education level and treatment variables: brand name/DCI, dose, formulation, posology for each medicament); pharmacists (socio-demographic characteristics: gender and year of birth and academic and work-related characteristics: role (manager/not manager), year of graduation in pharmacy, place of graduation in pharmacy, working hours in the CP) and CPs (average prescriptions per day, opening hours, location (urban/suburban/rural/industrial area), number of pharmacy technicians and pharmacists employed).

**Table 1 pone.0292037.t001:** Study outcomes.

Primary outcomes (type of variable)	Definition and assessment	Time point
Number of DRPs detected (quantitative)	DRPs associated with patients’ behavior detected by the pharmacist before the consultation (evaluation of the medication) and during the consultation (evaluation of patients’ information). Total number of DRPs and mean per patient and depending on the number of the patients’ medication will be calculated.	Pharmacists will complete the medication plan and PharmDISC tool before and during the consultation.
Evolution on the number of DRPs (quantitative)	Evolution on the number of DRPs associated with patients’ behavior detected will be assessed by comparing the differences between the three consultations with the patient.	Research team will calculate the differences using the medication plan at each consultation.
DRP classification (qualitative)	PharmDISC tool will be used for DRP related classification (15 DRPs related to patients’ behavior out of the 24 total DRP included in the tool): 1. Drug choice: duplicate, accumulation, adverse event. 2. Dose choice: under dose/overdose. 3. Drug use: a. inappropriate timing or frequency of administration, b. inappropriate use method, c. inappropriate treatment duration. 4. Patient: insufficient adherence, insufficient knowledge, burden due to therapy, inappropriate stockage, absence of label. 5. Logistics: prescribed drug not available, error in medication process. 6. Other (to be detailed by the pharmacist).	Pharmacists will complete the PharmDISC tool before and during the consultation.

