Number of pharmaceutical interventions (quantitative)	Number of interventions carried out by the pharmacist to correct DRPs and/or prevent their consequence. Total number of interventions and mean per pharmacist, per patient, per number of medications and number of DRPs identified will be calculated.	Pharmacists will complete the PharmDISC tool before and during the consultation.
Pharmaceutical interventions classification (qualitative)	Classification of interventions will be made using PharmDISC tool: • Substitution • Dose adjustment • Adjustment of the delivery amount (package size, quantity of packages, etc.) • Optimization of administration / Change of administration way • Therapy stopped/no delivery • Therapy started • Counselling of patient • Application/use instruction (training) • Delivery of an adherence aid inclusive counselling • Clarification in the case notes (history) • Information to the GP • Therapy monitoring • -Other	Pharmacists will complete the PharmDISC tool before and during the consultation.
Pharmaceutical interventions acceptance (quantitative)	Pharmaceutical interventions acceptance by the patient or the GP (when proposed to the GP, it will be considered as accepted unless the GP states otherwise). Number and proportion of intervention accepted versus proposed according to the number of medications and the number of DRPs.	Pharmacists will complete the PharmDISC tool during the second and third consultation.
**Secondary outcomes**	**Definition and assessment**	**Time point**
Number of removed medications (quantitative)	Expired or in bad condition or unused medications will be identified after reviewing the medication brought by the patient to the pharmacy: total number, mean per patient and percentage in relation to the total medication brought by the patient will be documented.	Pharmacists will complete the medication plan during the consultation with patients.
Number of removed medications discharged (quantitative)	Number of medications proposed to be removed and accepted by the patient after pharmacist-patient consultation: total number, mean per patient and percentage in relation to the total expired medication identified will be documented.	Pharmacists will complete the medication plan during the consultation.

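### The article gives inconsistent accounts of its primary outcome, and the analysis section does not name the powered contrast (change in DRPs from first to third consultation) as primary

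*Protocol article*

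**What the plan says.** The Protocol article describes its primary outcome in four places.

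- **Abstract, Methods:** "The primary outcome is the identification of DRPs associated to patients’ behavior". The next sentence lists the secondary outcomes, among them "number of expired medications, interventions carried out by pharmacists and pharmacists’ satisfaction".
- **Study measurements and outcomes, Table 1:** the heading is plural, "Primary outcomes (type of variable". Six rows follow before the secondary heading: number of DRPs, evolution of that number, DRP classification, number of interventions, intervention classification, and intervention acceptance. The first is "Number of DRPs detected (quantitative" and the fourth is "Number of pharmaceutical interventions (quantitative", each marked as quantitative.
- **Sample size:** "Primary objective of the study aims to measure the difference in DRPs per patient observed between consultations". The calculation targets a difference of 0.5 DRP per patient at the end of the study and is one-tailed, because a decrease is hypothesised.
- **Discussion:** "The study reports one primary outcome measure, the identification and management of DRPs related to patients with polypharmacy".

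Statistical methods and analysis then takes two differences per patient, second minus first and third minus first consultation. It applies them to a list that mixes variables from primary and secondary rows. The significance level is p<0.05. Two analysis sets are planned: complete cases, and the whole sample with baseline carried forward. Neither a contrast nor an analysis set is called primary.

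**The concern.** A reader cannot tell from the article which result decides whether the study met its primary aim. Interventions are primary in Table 1 and secondary in the Abstract. The Discussion counts one primary outcome where the table has six rows. The sample size supports one specific quantity, the end-of-study decrease in DRPs, but the analysis section does not single it out.

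As the text stands, a 6-month DRP change, a change in the number of interventions or an acceptance rate could each be presented as a primary result, and the document would offer a heading in support. None of these was the basis for the sample size. Acceptance is particularly exposed, because Table 1 counts a proposal to the GP as accepted unless the GP says otherwise.

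**Working it through.** **1. The statements side by side**

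| Place | Number of primary outcomes | Content | Status of interventions |
|---|---|---|---|
| Abstract | one | identification of DRPs | secondary |
| Table 1 | six rows | DRP count, evolution and type; intervention number, type and acceptance | primary |
| Sample size | one | decrease in DRPs per patient at end of study | not mentioned |
| Discussion | one | identification and management | part of management |

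The clear conflicts are the number of primary outcomes and the status of interventions. The sample-size quantity corresponds to Table 1 row 2 (evolution), made more specific.

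**2. The plan's own figure**

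Stated inputs: difference 0.5, one-sided 5%, power 0.80, intra-cluster correlation 0.02, 15% dropout, N = 162, 5 to 10 patients per pharmacy. The SD of the change is not given, so 162 can be neither confirmed nor refuted. The paired-change formula is n = (SD × (1.645 + 0.842) / 0.5)², multiplied by 1 + (m − 1) × 0.02 and divided by 0.85. Solved backwards:

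- Retained patients: 162 × 0.85 = 137.7.
- m = 5: design effect 1.08, effective n = 127.5, implied SD = 0.5 × √127.5 / 2.486 = 2.27.
- m = 10: design effect 1.18, effective n = 116.7, implied SD = 2.17.

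This places 162 on one one-sided contrast of one variable.

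**3. Two contrasts on the DRP count**

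Let Y1, Y2 and Y3 be the counts at the three consultations. Assume equal variance σ² and equal pairwise correlation ρ. Each difference from Y1 has variance 2σ²(1 − ρ), and the two differences have covariance σ²(1 − ρ). Their correlation is therefore 0.5. With both tested at 5%:

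- two-sided: 1 − P(|z1| < 1.96, |z2| < 1.96) = 9.1%;
- one-sided: 1 − P(z1 < 1.645, z2 < 1.645) = 8.8%;
- independence, for reference: 1 − 0.95² = 9.75%.

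**4. Adding the intervention outcomes**

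Two primary rows are classifications and yield no test of change. Four are quantitative, but DRP count and DRP evolution become the same variable once differences are tested. That leaves DRPs, number of interventions and acceptance. Three variables by two contrasts is six tests.

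- Six, independent: 1 − 0.95⁶ = 26.5%.
- Six, two-sided, equally correlated (simulated): 24% at 0.3, 21% at 0.5, 14% at 0.8.
- Table 1 records acceptance only at the second and third consultations, so contrasts with the first are doubtful for it. With one acceptance test there are five tests: 1 − 0.95⁵ = 22.6%. With none there are four: 1 − 0.95⁴ = 18.5%. Both assume independence.

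**5. Cost of keeping six co-equal primary tests**

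Bonferroni gives 0.05 / 6 = 0.0083 each. With the implied SD held fixed, one-sided power for the 0.5 effect is Φ(2.486 − 2.394) = 54% instead of 80%. Restoring 80% needs 162 × ((2.394 + 0.842) / 2.486)² ≈ 275 patients. One named primary contrast needs no adjustment and leaves N at 162.

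**The case against.** The best defence is that the Sample size section already identifies the main quantity. It calls the difference in DRPs the primary objective, says the calculation was based on that outcome, and gives an end-of-study time point and a direction. The Discussion's phrase repeats the study aim and can be read as one domain: the DRP rows are identification and the intervention rows are management. The study is single-arm, partly descriptive by its own objective, and open about lacking a control group.

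Much of this stands. It rules out four stronger readings that a reader might reach.

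- *The sample size introduces a separate fourth outcome.* It does not; it is Table 1 row 2 with a time point and direction.
- *Either a rise or a fall in DRPs would count as success.* One might infer this because identification suggests that more is better. But the only stated hypothesis is a decrease, the count row describes totals and means, and nowhere is a higher count called success.
- *False positives are uncontrolled.* A multiplicity rule or test order may sit in an analysis plan that is not shown. Its absence from a condensed article is not an error.
- *The false-positive risk is 26%.* That assumes independence, although interventions are made to correct DRPs and so the counts are linked. It also counts two contrasts for acceptance.

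The defence does not remove the conflict over interventions between the Abstract and Table 1, or the mismatch between one outcome and six rows. Nor does it supply a primary contrast in the analysis section.

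**Conclusion.** The article is inconsistent about its primary outcome, and its analysis section does not carry forward the contrast that was powered. This is a contradiction within current text and does not depend on anything left to an analysis plan.

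The firm size is about 9% family-wise error for the DRP count alone if both contrasts are treated as primary (9.1% two-sided, 8.8% one-sided). It rests on equal variances and equal correlations across consultations. If intervention outcomes are also treated as primary the figure is higher, by an amount that depends on unknown correlations; 26% is a ceiling only.

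I rate this as should-fix. The powered quantity, its direction and its time point are already in the document, so the task is to make the other sections agree with them.

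**What to change.** - **Primary outcome:** name one, the mean within-patient change in the number of behaviour-related DRPs from the first to the third consultation. Test it with the sidedness used in the Sample size section, in one named analysis set (complete cases or the whole sample), with the other as a sensitivity analysis.
- **Secondary:** the second-versus-first change in DRPs, and the number and acceptance of interventions.
- **Descriptive:** the DRP count at each consultation, the DRP classification and the intervention classification.
- **Agreement:** edit the Abstract, Table 1, Statistical methods and analysis, and the Discussion so that all give this one primary outcome.
- **Disclosure:** data collection began in April 2023, so relabelling listed primary outcomes should be reported as a dated clarification, with the reason that it aligns the text with the sample-size basis. The registry entry is not at hand; if its list differs, it needs the same update.

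The cost is text edits and the dated disclosure. Data collection, the intervention and the target of 162 patients do not change. The edits should be in place before the analysis planned for summer 2024.
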